#### Economic analyses

Health-care costs will be measured using the Tic-P. Total costs are
calculated by using an update of the Dutch manual for costing in economic
evaluations [68]. Clinical outcomes
12 months after the start of treatment will be used in the economic
evaluation. Student’s *t*-test for statistical significance
will be used to measure differences between MRT and CBT. Fatigue severity
during 1 year of follow-up will be used as the primary outcome measure for
cost-effectiveness.

A cost-utility analysis will be performed by relating the mean total costs to
the mean health utility (EQ-5D) scores of both groups. The costs per QALY of
both treatments will be compared. Our primary (base-case analyses) will be
performed according to the intention-to-treat principle, including data from
all participants regardless of whether they received the intervention or
not. For the analyses we will use SPSS statistical software and Excel (for
the bootstraps).

Respondents for whom at least 75% of the data per measurement instrument are
available will be included in the analysis. Missing data on item level will
be handled using SPSS missing value analysis. Completely missing
measurements will be handled using multiple imputation (MI). A baseline
analysis will be performed to examine the comparability of groups at
baseline for both costs and outcomes. If necessary, methods will be applied
to control for differences in baseline [71]. To investigate whether data are normally
distributed, a Kolmogorov-Smirnov test will be performed. Despite the usual
skewness in the distribution of costs, the arithmetic means will be
generally considered the most appropriate measures to describe cost data
[72,73]. Non-parametric bootstrapping is a method based on
random sampling with replacement based on individual data of the
participants [74]. The bootstrap
replications will be used to calculate 95% confidence intervals around the
costs (95% CI), based on the 2.5th and 97.5th percentiles. If cost data are
distributed normally, *t*-tests will be used.

The incremental cost-effectiveness ratio (ICER) will be determined on the
basis of incremental costs and the effects of the MRT in comparison with
CBT. The cost-effectiveness ratio will be expressed in terms of costs per
unit of outcome; the cost-utility ratio will focus on the incremental cost
per QUALY gained. The robustness of the ICER will be checked by
non-parametric bootstrapping. Bootstrap simulations will also be conducted
in order to quantify the uncertainty around the ICER, yielding information
about the joint distribution of cost and effect differences. The
bootstrapped cost-effectiveness ratios will be subsequently plotted in a
cost-effectiveness plane in which the vertical line reflects the difference
in costs and the horizontal line reflects the difference in effectiveness.
The choice of treatment depends on the maximum amount of money the society
is prepared to pay for a gain in effectiveness, which is called the ceiling
ration. Therefore, the bootstrapped ICERs will also be depicted in a
cost-effectiveness acceptability curve showing the probability that MRT is
cost-effective using a range of ceiling ratios. Additionally, to demonstrate
the robustness of our base-case findings, a multi-way sensitivity analysis
will be performed.

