### Assessment and procedures

After inclusion, the research assistant contacts the patient to make an
appointment for the baseline assessment (T1). During T1 the patient is asked to
wear the activity monitor for one week and to fill in the following
questionnaires: 

 Checklist Individual Strength (CIS)

 Short Form 36 (SF-36)

 EuroQol- 5D (EQ-5D)

 Symptom Check List-90 (SCL-90)

 Self-Efficacy Scale-28 (SES 28)

 Causal Attribution List (CAL)

 Mindfulness Attention Awareness Scale (MAAS)

 Sickness Impact Profile-8 (SIP-8)

 Life Satisfaction Questionnaire, Dutch Version (LSQ-DV)

The patient is instructed on how to fill in the Tic-P, part II on health- and
non-health-related costs every month for 1 year. One week after baseline
assessment, the research assistant collects the activity monitor. The research
assistant gives the patient a blind envelope with the treatment conditions.
Treatments start within 4 weeks. Two weeks after the start of treatment, a
patient is asked to fill in the list of Borkovec and Devilly and the PSCG, part
1. At 3 and 9 months after T1 a patient is asked to fill in the Tic-P, part I at
home. Six months after the start of treatment the research assistant assesses
the patient again (T4). The patient is asked to wear the activity monitor and
fill in the same questionnaires as in T1 completed by the PSCG, part II
self-rated improvement questionnaire and Tic-P, part I. Twelve months after the
start of the treatment, the same assessment as in T4 will be repeated (T5). For
each patient the study takes 12 months.

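### The economic analysis adjusts for baseline only conditionally although the efficacy model always does, plans a baseline cost comparison with no cost form listed at T1, and mixes two clocks in its health-care cost forms

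*Protocol article*

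**What the plan says.** All references are to the protocol article.

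- **Efficacy.** Analyses of efficacy specifies mixed linear regression of the follow-up value, with the baseline value of the same outcome as a covariate in every case.
- **Economic comparison.** Economic analyses says that Student's t-test "will be used to measure differences between MRT and CBT", without naming covariates. Further on, the t-test for costs becomes conditional: if cost data are "distributed normally, *t*-tests will be used". Bootstrap "replications will be used to calculate 95% confidence intervals around the" costs, and the ICER, the cost-effectiveness plane and the acceptability curve are also bootstrapped.
- **Baseline.** The same section plans to examine comparability at "baseline for both costs and outcomes. If necessary, methods will be applied" to control for differences. It gives a citation but no trigger.
- **T1 forms.** Assessment and procedures lists nine T1 questionnaires, including the CIS and the EQ-5D. None is a cost form. At T1 the patient is only instructed on Tic-P part II.
- **Timing.** "At 3 and 9 months after T1 a patient is asked to fill in the Tic-P", part I. The other two part I forms belong to T4 and T5: "Six months after the start of treatment the research assistant assesses" the patient for T4, and T5 follows twelve months after treatment start. The allocation envelope is handed over when the activity monitor is collected, one week after T1, and "Treatments start within 4 weeks".

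**The concern.** Fatigue severity is both a primary efficacy outcome and the primary effect measure for cost-effectiveness, and cost-effectiveness is itself one of the primary objectives in Aims of the study. If one section always adjusts and the other adjusts only after looking, the trial can report two fatigue effects from the same patients. The effect in the ICER denominator would then be the less precise of the two. Whether to adjust also becomes a decision taken after the baseline data are seen.

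QALYs are more exposed than a single follow-up score, because the baseline EQ-5D value enters the QALY directly.

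The baseline cost comparison cannot be carried out from the forms listed. The mixed clocks mean that forms intended to be three months apart are not, so health-care costs may be missed in some weeks and counted twice in others.

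**Working it through.** The economic section states no numerical figure to reproduce. The correlation, the EQ-5D SD, the QALY rule and the recall period below are assumptions, because the article does not give them.

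**1. Precision lost without adjustment.** With baseline-follow-up correlation r, the adjusted variance is (1 − r²) times the unadjusted one, so the unadjusted variance is 1/(1 − r²) times the adjusted one.

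- r = 0.3: 1/0.91 = 1.10
- r = 0.5: 1/0.75 = 1.33
- r = 0.7: 1/0.51 = 1.96

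**2. Chance imbalance in fatigue.** With 48 evaluable patients per arm (Sample size section), the SE of the baseline difference is √(2/48) = 0.204 SD. A 1-SE imbalance shifts an unadjusted follow-up difference by r × 0.204 SD, that is 0.06, 0.10 or 0.14 SD at r = 0.3, 0.5 or 0.7. If the follow-up SD equals 5.9, the top of the stated baseline range, the shift is 0.3 × 0.204 × 5.9 = 0.36, 0.5 × 0.204 × 5.9 = 0.60 or 0.7 × 0.204 × 5.9 = 0.84 CIS points. The planned clinically relevant difference is 3.0 points.

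**3. Chance imbalance in QALYs.** Assume an EQ-5D SD of 0.25, 60 patients per arm and the trapezoid rule over T1, 6 and 12 months.

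- SE of the baseline utility difference: 0.25 × √(2/60) = 0.046.
- T1 weight: half of the first half-year, 0.5 × 0.5 = 0.25.
- Direct contribution of a 1-SE imbalance: 0.25 × 0.046 = 0.011 QALY.
- Upper bound, if the imbalance persisted in full for the year: 0.046 QALY.

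**4. Cost-form timing.** Let L be the lag in weeks from T1 to treatment start. The envelope comes one week after T1 and treatment follows within four weeks, so L is about 1 to 5. Part I forms fall at weeks 13, 26 + L, 39 and 52 + L after T1. The intervals are therefore 13, 13 + L, 13 − L and 13 + L weeks. With an assumed 13-week recall, the two long intervals leave 2L weeks uncovered and the short one counts L weeks twice.

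| L (weeks) | Intervals (weeks) | T1 to T5 | Uncovered | Counted twice |
|---|---|---|---|---|
| 0 (one clock) | 13, 13, 13, 13 | 52 | 0 | 0 |
| 1 | 13, 14, 12, 14 | 53 | 2 | 1 |
| 4 | 13, 17, 9, 17 | 56 | 8 | 4 |
| 5 | 13, 18, 8, 18 | 57 | 10 | 5 |

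The intervals follow from the article and L. The last two columns depend on the recall assumption.

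**5. Baseline costs.** Economic analyses requires a comparison of costs at baseline. Assessment and procedures places the first part I form three months after T1. Cost analysis says that health-care costs are recorded every three months, which does not exclude a T1 form, but none is listed.

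**The case against.** **The t-test is not the economic comparison.** A reader might infer that it is, but the article does not support that. Cost intervals, the ICER and the acceptability curve are bootstrapped, and deleting the t-test would leave the ICER unchanged. This stands. The remaining fault is that the t-test appears first without condition and later only for normally distributed costs. Bootstrapping unadjusted means also carries the same imbalance.

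**Baseline control is planned, and its trigger is detail for the full protocol or SAP.** This is partly right. No trigger is stated, so one may not assume a significance test that would overlook moderate imbalance. Nor is an unadjusted comparison biased over repeated randomisations. But making adjustment conditional is a choice the article does fix. It departs from the article's own efficacy model and gives up precision that data already collected would provide.

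**Costs are not simply timed from T1 with effects timed from treatment start.** That stronger reading fails. The T4 and T5 cost forms are completed at the visits that supply the effects, so the documents do not support saying that the ICER's numerator and denominator cover wholly different periods. The inconsistency lies within the cost schedule. The starting point of the monthly part II year is not stated; T1 is only implied by the instruction given there.

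**Ten weeks lost and five counted twice is not a fact about the trial.** It is the worst case under an assumed recall period. Other records may narrow the gap. Therapists register treatment hours session by session, so the cost of MRT and CBT themselves does not depend on patient recall. Assessment and procedures also describes monthly part II as covering health-related costs, although Cost analysis splits the content differently. Nothing shows that the lag differs between arms.

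**Conclusion.** The point holds in three limited parts.

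- **Conditional adjustment.** The economic analysis adjusts for baseline only conditionally where the efficacy analysis always does. The cost is an effect variance 1.10 to 1.96 times the adjusted one for assumed correlations of 0.3 to 0.7. Under the stated assumptions, a 1-SE chance imbalance in EQ-5D adds 0.011 QALY directly, with 0.046 as the upper bound.
- **Baseline costs.** The planned comparison has no listed data source at T1. This rests on no assumption beyond the T1 list being complete.
- **Mixed clocks.** Part I intervals range from 13/14/12/14 weeks at a 1-week lag to 13/18/8/18 weeks at a 5-week lag. Uncovered time of 2 to 10 weeks and double counting of 1 to 5 weeks follow only if recall is three months.

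None of this shows that the cost-effectiveness conclusion would change. It should still be corrected: it concerns a primary objective, and the remedy for the first part uses data already in hand.

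**What to change.** 1. Delete the condition on baseline adjustment and the unconditional t-test. Estimate the incremental fatigue effect and incremental QALYs by regression, always adjusted for T1 CIS-fatigue or T1 EQ-5D respectively and for centre. Refit within each bootstrap replicate, so that the ICER's fatigue effect is adjusted for baseline in line with the efficacy model.
2. Drop the baseline cost comparison. Trial status says that data collection is complete, so a T1 cost form cannot be added.
3. Use the recorded form dates to place costs on the same 12-month window as the effects. Remove overlapping weeks and treat uncovered weeks as missing for the multiple imputation already planned. State the Tic-P recall period and where the part II year begins, and reconcile the two descriptions of part II. New visit dates cannot be created for patients who never started treatment; the recorded dates have to serve.

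The cost is a little more programming. The article plans the bootstraps in Excel, where refitting a regression in every replicate is awkward, so a scripted bootstrap is likely to be needed. No new data are required.

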#### Mediation analyses

In the mediation analysis, we investigate whether self-efficacy, somatic
attributions and/or present-centred attention-awareness intervenes in the
relationship between treatment and outcome. Multiple regressions are used to
explore which factors mediate the outcome. Mediation is suggested when the
change in the putative mediating factors is significantly related to
treatment as the independent variable, outcome is significantly related to
treatment as the independent variable, and finally, the relationship between
outcome and treatment decreases (or goes to zero) when the change in the
mediation factor is entered into the equation [66].

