#### Mediation

In order to understand how treatment works, mediation analyses are performed.
Two studies on mediation could not confirm the mediating role of physical
activity in reducing fatigue in CFS. Moss-Morris (2005) [21] investigated physical activity as a
mediator in the treatment effect of GET and Wiborg (2010) [65] in CBT. Since physical activity does
not mediate the outcome, other parameters have to be responsible for a
decrease of fatigue during therapy. In the model of Vercoulen et al.
[14], somatic attributions,
focussing on pain and fatigue, and low self-efficacy contribute to the
perpetuating of CFS complaints. Patients with CFS feel helpless and
surrendered to their complaints, making it difficult to change their
situation. During therapy patients learn to change cognitions into more
helpful cognitions, which increases self-efficacy. They learn to accept
their situation in the present, making choices based on helpful cognitions
and bodily symptoms other than pain and fatigue, and learn to focus on
getting better instead of focussing on complaints and somatic attributions.
Our hypothesis is that by increasing self-efficacy, decreasing somatic
attributions and increasing the present-centred attention-awareness during
activities first, behavioural changes can be made based upon these changes
and eventually the severity of fatigue will decrease.

There are no studies that we are aware of that determine the mediating role
of self-efficacy, somatic attributions and present-centred
attention-awareness. Mediation will be investigated by the three-step method
described by Baron and Kenny [66].
Before treatment (T1), 6 and 14 weeks after start of treatment (T2, T3),
CIS, SE28, CAL and MAAS are filled in by the patient in order to analyse
mediation at different moments during treatment phase.

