### Analyses

#### Sample size

Based on the available literature [25,34,69] and our pilot
study, mean CIS-fatigue scores at the start of CBT or multidisciplinary
rehabilitation are about 50–52 with a standard deviation of 3.9-5.9.
Following previous trials [28,34], we assume that a difference of 0.5 SD of the
mean group score at baseline is clinically relevant. This equals a
difference of about 3.0 points on the CIS fatigue scale. With a sample size
of 48 patients in each treatment arm, accepting an alpha error of 0.05 and a
power of 0.80, it is possible to measure a minimal difference of 3.0 points
on the CIS fatigue scale. To compensate for an estimated 25% dropout rate, a
total of 120 people will be included.

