#### Analyses of efficacy

The effects of therapy conditions on the various outcomes will be compared
using an ‘intention to treat’ approach. Data will be analysed
with mixed linear regression models. The follow-up measurement will be the
dependent variable, and the baseline value of the particular outcome will be
added as covariate as well as random intercepts for individuals to allow for
dependence within patients and centres [70]. Effect modification will be evaluated by
introducing interactions between therapy condition and the potential
modifiers in the equation. There will be a post-hoc analysis of the
non-response group and the missing values. Dropout patients will be asked
about the reason for stopping treatment or not attending a measurement.
Patient characteristics of the dropouts will be compared to those of the
group that completed each treatment. For the analyses we will use SPSS
statistical software.

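### The treatment-to-mediator test is set on the mediator's raw change without naming its T1 value as covariate, which gives away power at a significance gate

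*Protocol article*

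**What the plan says.** The section *Mediation analyses* gives three conditions. The first is that the "change in the putative mediating factors is significantly related to treatment as the independent variable". The second is a significant treatment-outcome relationship. The third is that this relationship shrinks "when the change in the mediation factor is entered into the equation". The mediator is thus written as a change score in the first and third conditions. Treatment and mediator change are the only predictors named. The section says multiple regressions will be used, but it neither lists nor excludes further covariates. It does not say whether the outcome is a follow-up score or a change.

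The section *Mediation* under *Outcome measures* has the CIS and the three mediator questionnaires completed before treatment and again at 6 and 14 weeks. *Assessment and procedures* confirms that they belong to the T1 assessment. For efficacy, the article models the follow-up score and states that "the baseline value of the particular outcome will be added as covariate".

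**The concern.** The article treats baseline in two ways and gives no reason for the difference. A raw change score is negatively related to its own baseline, so part of its spread only reflects where each patient started. Regressing the change on treatment alone leaves that spread in the error term. A chance difference between arms at T1 also passes into the estimated arm difference in change.

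Secondary objective 3 is answered by this rule, and its first condition is pass or fail on significance. Low power there means that a real mediator is more likely to be dropped before the later conditions are considered.

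**Working it through.** **Inputs**

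- 48 patients per arm and alpha 0.05, from *Sample size*. The article does not state sidedness; two-sided is assumed.
- 45 per arm as a check: the planned 120 less the article's own 25% dropout is 120 × 0.75 = 90.
- Arm difference in the mediator: 0.5 SD. This is an assumption. The article uses 0.5 SD for fatigue and gives nothing for the mediators.
- Correlation ρ between baseline and follow-up mediator: not given, so taken over 0.3 to 0.8, with equal SDs at both times.

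**The plan's own figure.** No power is stated for mediation. The 48 per arm belongs to CIS fatigue, where with "power of 0.80, it is possible to measure a minimal difference of 3.0 points". Using n = 2(z₁ + z₂)²(SD/3.0)², 48 is reached one-sided with SD 5.9: 2 × (1.645 + 0.842)² × (5.9/3.0)² = 47.8. It is also reached two-sided with an SD of about 5.2. Two-sided with SD 5.9 gives 61. That is a separate matter; 48 serves here only as the group size.

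**Variances**, in units of the mediator's SD²:

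- raw change: 2(1 − ρ)
- follow-up adjusted for T1: 1 − ρ²
- excess carried by raw change: 2(1 − ρ) − (1 − ρ²) = (1 − ρ)²
- proportional saving from adjustment: 1 − (1 + ρ)/2 = (1 − ρ)/2

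**Power.** This is from the noncentral t distribution, with noncentrality (0.5/SD) × √(n/2). At n = 48, √24 = 4.899. For ρ = 0.5, raw change has variance 1.00 and noncentrality 0.5 × 4.899 = 2.449. Adjusted, the variance is 0.75, the SD 0.866 and the noncentrality 2.828.

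| ρ | variance, raw change | variance, adjusted | saving | power, raw change (48 per arm) | power, adjusted (48 per arm) | power, raw vs adjusted (45 per arm) |
|---|---|---|---|---|---|---|
| 0.3 | 1.40 | 0.91 | 35% | 54% | 72% | 51% vs 69% |
| 0.5 | 1.00 | 0.75 | 25% | 68% | 80% | 65% vs 77% |
| 0.7 | 0.60 | 0.51 | 15% | 88% | 92% | 86% vs 91% |
| 0.8 | 0.40 | 0.36 | 10% | 97% | 98% | 96% vs 97% |

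The degree of freedom spent on the covariate changes these figures by about 0.1 percentage point at most.

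**Change or follow-up as dependent variable.** Once the T1 mediator is a covariate, regressing the follow-up mediator or its change on treatment gives the same treatment coefficient and standard error. Only the coefficient of the T1 value differs, by exactly 1. The article's wording in terms of change can therefore stay.

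**The case against.** **The article is condensed.** Multiple regression leaves room for covariates, and a covariate list is commonly left to a fuller plan. A reader might infer that the mediation models contain no baseline covariates at all; the text does not say so. That part of the objection stands. What remains is that the change score is written positively, with treatment as the only predictor named for the first step.

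**A change score is not an error.** This also stands: objective 3 is itself worded in changes, and randomisation protects the arm comparison. The loss is one of precision only and is small when ρ is high.

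**The last step.** A reader might infer that raw change there creates false mediators. The documents do not support that.

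- Simulation with a mediator that has no effect (ρ 0.5, baseline mediator-fatigue correlation −0.4, arm effects of 0.5 SD on the mediator and −0.5 SD on fatigue, no baseline terms) makes the mediator coefficient significant in 15 to 19% of trials with 45 to 60 per arm. This is not a false-mediation rate. The article's rule looks for a smaller treatment coefficient, not a significant mediator coefficient.
- In that scenario the treatment coefficient moves by about 0.05 SD, or 0.3 CIS points at SD 6. With a follow-up outcome it grows, from −0.50 to about −0.55. Only with a change outcome does it shrink, to about −0.45.
- Adding the T1 outcome alone, as the efficacy model does, returns the rejection rate to about 5%.

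**Replacing mediator change in the last step by the follow-up mediator plus its T1 value is not uniformly better.** If stable patient traits link mediator and fatigue (same correlations, no mediator effect), that model, with the T1 outcome included, makes the mediator significant in 37% of trials at 48 per arm, against about 5% for raw change. If instead the mediator's level acts on the outcome with true coefficient −0.40, raw change plus T1 outcome recovers only −0.20 to −0.24. The mediator is not randomised, and the data cannot settle which model is right.

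**Conclusion.** The point holds for the treatment-to-mediator step. Raw change with no T1 mediator named is unbiased but less precise than the baseline-adjusted comparison at any correlation below 1. The loss is about 18 percentage points of power at an assumed correlation of 0.3, 12 at 0.5, between 4 and 5 at 0.7 and about 1 at 0.8. These figures assume a 0.5 SD arm difference, equal SDs at both times, 48 per arm and two-sided testing.

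For the last step, only a clarification is warranted: that the T1 outcome enters both outcome regressions. No claim of spurious mediation is made out. The objective is secondary and exploratory, and the primary comparison is unaffected, so this is a minor improvement.

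**What to change.** In *Mediation analyses*:

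1. Analyse each mediator at T2 or T3 (or its change from T1) on treatment, with the T1 value of that mediator as covariate.
2. Include the T1 value of the outcome in both outcome regressions, in line with *Analyses of efficacy*. Fit the models with and without the mediator on the same patients with otherwise the same covariates, so that the two treatment coefficients can be compared.
3. Mediator change may stay in the last step. If the follow-up mediator with its T1 value is used there, label it a sensitivity analysis at most and state the assumption behind each form.

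The cost is a sentence or two and one or two degrees of freedom per regression. All T1 values are already scheduled before the allocation envelope is handed over.

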### Aims of the study

The FatiGo trial is designed to address the following primary objectives:

 1. To assess the differences in treatment effect (change between baseline and
6-month follow-up in fatigue severity and quality of life) in patients with CFS
between individual multidisciplinary rehabilitation treatment (MRT) and
individual cognitive behavioural therapy (CBT).

 2. To assess the differences in long-term treatment effect (change between
baseline and 12-month follow-up in fatigue severity and quality of life) in
patients with CFS between the two treatments.

 3. To assess the difference in cost-effectiveness and cost-utility between MRT
and CBT from both a health care and societal perspective at 12-month
follow-up.

 4. To assess the differences in treatment effect in psychological symptoms,
self-efficacy, causal attributions, present-centred attention-awareness, impact
of disease on physical and emotional functioning, self-rated improvement and
life satisfaction between MRT and CBT (at 6- and 12-month follow-up).

The secondary objectives of this trial are:

 1. To assess the influence of patients treatment expectancy and credibility on
the effectiveness of treatment.

 2. To assess what baseline factors (other than the assigned treatment) predict a
change in fatigue and increase in quality of life in all participants.

 3. To evaluate whether changes in self-efficacy, changes in causal attributions
and/ or changes in present-centred attention-awareness (at baseline, 6 and 14
weeks after start of treatment) mediate changes in fatigue severity and changes
in quality of life after treatment.

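### The mediation rule is worded for one factor, with no joint model, so it cannot separate which of three related factors mediates: a correlated bystander can be credited with part of the true mediator's effect

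*Protocol article*

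**What the plan says.** Under Aims of the study, the third secondary objective asks whether changes in self-efficacy, causal attributions and/or attention-awareness "mediate changes in fatigue severity and changes in quality of life after treatment". The Mediation section under Outcome measures says: "Mediation will be investigated by the three-step method". It presents the factors as parts of one process, for example: "During therapy patients learn to change cognitions into more helpful cognitions, which increases self-efficacy".

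The section Mediation analyses puts the question in terms of all three: "we investigate whether self-efficacy, somatic attributions and/or present-centred attention-awareness intervenes in the relationship between treatment and outcome". It continues: "Multiple regressions are used to explore which factors mediate the outcome". It then gives three conditions:

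1. The "change in the putative mediating factors is significantly related to treatment as the independent variable".
2. The "outcome is significantly related to treatment as the independent variable".
3. Finally, "the relationship between outcome and treatment decreases (or goes to zero) when the change in the mediation factor is entered into the equation".

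The third condition speaks of the mediation factor in the singular. Nowhere does the article describe a regression that contains the three changes together, or one factor adjusted for another.

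**The concern.** The question is comparative (which of three), but the decision rule looks at one factor at a time on its natural reading. The article's own account makes correlated changes likely: cognitions change, self-efficacy rises, somatic attributions fall and awareness grows within the same therapy. In a regression with treatment and one factor, the slope of that factor also carries the effect of any correlated factor left out. A factor that does nothing itself can then lower the treatment coefficient and meet all three conditions.

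The trial could therefore name two or three mediators when one is at work, and could not say which factor carries the effect. That is what the third secondary objective is meant to establish.

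**Working it through.** The mediation sections state no figure, so there is none to reproduce. The check is algebra followed by simulation.

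**Inputs.** From the Sample size section: 48 per arm and alpha 0.05 (taken as two-sided; the article does not say). Everything else is assumed, because the article gives no correlations and no effects on the factors. M is the true mediator and P is a bystander with no effect on the outcome. Treatment shifts each by 0.5 SD. The slope of M on the outcome is 0.5, the direct treatment effect is 0.25 SD, and the within-arm SD of the outcome is 1. The within-arm correlation of M and P is rho = 0, 0.3, 0.5 or 0.7. Total treatment effect = 0.25 + 0.5 × 0.5 = 0.50. True indirect effect through M = 0.5 × 0.5 = 0.25.

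**Algebra.** With P entered alone, the expected fall in the treatment coefficient is

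(effect of treatment on P) × rho × (slope of M).

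At rho = 0.5 this is 0.5 × 0.5 × 0.5 = 0.125. That is 25% of the total effect (0.125/0.50) and half of the true mediator's share (0.125/0.25), for a factor that does nothing. With M and P entered together, the part assigned to P has expectation 0.

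**Simulation**, 4000 trials per setting (Monte Carlo standard error at most √(0.25/4000) = 0.8 percentage points). Entries are the share of all trials in which P is credited:

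| Rule applied to P | rho 0 | rho 0.3 | rho 0.5 | rho 0.7 |
|---|---|---|---|---|
| Three conditions as written, P alone | 23% | 44% | 48% | 51% |
| P alone, both paths tested | about 3% | 22% | 46% | 63% |
| M and P together, both paths tested | about 3% | about 3% | about 3% | about 3% |

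Both paths tested means that treatment is significantly related to P, and P is significantly related to the outcome given treatment. The true mediator M is detected in 68%, 66% and 67% of trials singly and in 68%, 66% and 65% jointly (rho 0.3, 0.5, 0.7), so joint entry costs it at most about two points.

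**Two separate sources of false credit.** At rho = 0 no other mediator confounds P, yet the written rule still credits it in 23% of trials. That comes from the third condition asking only for a decrease, without a test. Testing the paths removes that part (about 3%) but leaves 46% at rho = 0.5. Only joint entry removes the remainder.

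**Sensitivity to the assumptions.** With 0.7 SD shifts and the same slope and total effect, the fall at rho = 0.5 is 0.7 × 0.5 × 0.5 = 0.175 of 0.50 (35%). The written rule then credits P in 32%, 58%, 64% and 64% (rho 0 to 0.7), against about 3% jointly. If P differs by arm only because it follows M, the figures are 11%, 31% and 49% (rho 0.3, 0.5, 0.7), against 0.8%, 1.5% and 2.8% jointly. If P does not differ by arm at all, the first condition holds false credit to 2.6% (rho 0.5).

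**The reverse case.** Suppose attributions act on the outcome only through self-efficacy (treatment shift 0.7 SD, self-efficacy slope 0.5, link 0.3, 0.5 or 0.7). Attributions are then a genuine upstream mediator. Single-factor models with both paths tested detect them in 27%, 65% and 86% of trials; the joint model does so in about 5% each time.

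**The case against.** Four points can be made for the plan.

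First, entry one at a time is inferred. The term multiple regressions can mean several predictors in one model, the factors are elsewhere named in the plural, and the singular stands in a generic definition taken from the cited method. This stands as a limit on the reading: a reader might infer that the article prescribes separate entry, and it does not say so. It does not say joint entry either, and the singular points the other way.

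Second, a condensed article may leave model detail to the analysis plan. That would answer a mere omission. Here the article states a decision rule, and that rule does not fit the question set just before it.

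Third, the aim is secondary and the wording cautious: factors are explored and mediation is suggested. This stands, and it limits the weight of the point.

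Fourth, a joint model is not a neutral replacement. The article describes changed cognitions raising self-efficacy, which is a chain, and the reverse case above shows that joint entry then misses a real upstream factor. This stands in full. It is why the joint model should be added beside the single-factor models and not displace them.

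**Conclusion.** The point holds: the stated rule cannot tell a mediator from a correlated bystander. Under the main assumptions, single-factor models credit the bystander in about 22% to 63% of trials even when both paths are tested, against about 3% jointly. The size depends on the assumed correlations and effects, and on the bystander differing by arm.

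Three stronger readings are not supported. A reader might infer that a bystander almost always passes. That is so only among trials that already meet the first two conditions (92% to 100%); over all trials it is about 44% to 51%, and part of that is due to the untested decrease. A reader might infer that the bystander takes over the true mediator's whole effect; at correlation 0.5 it takes about half on average. A reader might infer that joint entry alone gives the right answer; it does not settle causal order among factors that influence one another.

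The primary comparison of treatments is not affected. The change is worth making because the third secondary objective depends on it.

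**What to change.** In Mediation analyses, keep the single-factor models and add, for each outcome and time point, one model containing treatment and the changes in self-efficacy, physical attributions and attention-awareness together. Report each factor's specific indirect effect with a 95% bootstrap interval next to its single-factor result. State that a factor is said to mediate independently of the others only where the joint model supports it. Where a factor is supported only in its single-factor model, say that the data cannot separate a bystander from a factor acting through another one. If joint entry was intended all along, the section should say so.

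The cost is a few sentences and additional regressions on data already collected; Trial status places the analysis still ahead. Intervals for each factor will be somewhat wider if the changes are strongly correlated, and the joint model gives little credit to a factor that works through another, which is the reason for reporting both.
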